#### Exclusion criteria for healthy subjects

Those who have been diagnosed as esophageal diseases such as NERD, RH, and BE.Patients with organic lesions such as upper gastrointestinal bleeding or operation, esophageal stricture, esophageal, and gastric tumors.Patients with serious primary diseases such as cardiovascular, cerebrovascular, liver, kidney, and hematopoietic system.Women who are breastfeeding, pregnant, or preparing for pregnancy.Patients with anxiety or depression.Those who with a history of mental or neurological disorders/diseases.Patients who have participated in any other clinical trials within 3 months.

### Sample size {14}

According to clinical experience, the effective rate of NERD in the TCM group was P1 = 92.0%. The NERD effective rate of the western medicine group was P2 = 61.2% [(two-sided type I error rate of 0.05, *α* = 0.05); (one-sided type I error rate of 0.20, *β* = 0.20)]. The sample size is calculated by the following formula:
$$ n=\frac{2\overline{p}\overline{q}{\left({Z}_{\alpha }+{Z}_{\beta}\right)}^2}{{\left(P1-P2\right)}^2} $$

*n*1 = *n*2 = 2 × 0.766 × 0.234 × 2.8^2^ ÷ 0.308^2^ = 30. Taking approximate dropouts of 20% into account, the number of participants recruited was estimated to be 36 per group. Therefore, a total of 72 patients will be recruited in this trial. And we will additionally recruit 10 healthy controls.

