## Methods/design

### Study design and setting {8-9}

This is a single-center, double-blinded, placebo-controlled, randomized controlled trial (RCT), which will be conducted in Dongfang Hospital, Beijing University of Chinese Medicine. The study is conducted in accordance with the Declaration of Helsinki (Edinburgh 2000 version). The final protocol (Version 2.0, 11 November 2020) of this trial has been approved by Ethical Committee of Dongfang Hospital, Beijing University of Chinese Medicine (Version number: JDF-IRB-2020033602). In addition, this trial has been registered in the Chinese Clinical Trial Registry (No. ChiCTR2000041225, registered on 22 December 2020).

We aim to enroll 72 patients with NERD over a 2-year period (Date from November 2020 to December 2022) from the department of gastroenterology in Dongfang Hospital, Beijing University of Chinese Medicine. Eligible patients will be randomized at a ratio of 1:1 to either TCM group (HWJNR with omeprazole enteric-coated tablets placebo) or western medicine group (omeprazole enteric-coated tablets with HWJNR placebo) for 8 weeks treatment. At the end of this trial, the primary outcome (GERD-Q) and the secondary outcome (SF-36, PRO, syndrome score of TCM) will be evaluated. We will obtain peripheral venous blood, urine, and stool from NERD patients before and after treatment. This study involves 3 site visits (week 0, week 4, and week 8) and 10 call visits (weekly call during the treatment period and follow-up at month 1 and month 3). The process of the study is schematically shown in Fig. 1. And we will additionally recruit 10 healthy controls.

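### The 20% dropout allowance is computed as 30 × 1.2 = 36 per group; 36 covers about 17% loss, and the effect on power is about one point

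*Protocol article*

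**What the plan says.** The protocol article, under Sample size {14}, assumes that "the effective rate of NERD in the TCM group was P1 = 92.0" per cent and that "The NERD effective rate of the western medicine group was P2 = 61.2" per cent. It takes a "two-sided type I error rate of 0.05" and sets β = 0.20. It describes β as a "one-sided type I error rate of 0.20", which can only mean a type II error rate, hence 80% power. The substitution is printed as "2 × 0.766 × 0.234 × 2.8^2^ ÷ 0.308^2^ = 30" per group.

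The dropout step follows: "Taking approximate dropouts of 20% into account, the number of participants recruited was estimated to be 36 per group". The inflation itself is not written out. The section concludes that "a total of 72 patients will be recruited in this trial". Study design and setting {8-9} repeats the total: "We aim to enroll 72 patients with NERD over a 2-year period".

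**The concern.** The section gives three figures that should fit together: 30 needed per group, about 20% expected to drop out, and 36 recruited per group. They do not fit. Adding 20% of the required number is not the same as recruiting enough to have the required number left after 20% are lost. A reader would take the sentence to mean that 20% attrition still leaves 30 per group, and it does not.

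At stake is whether a stated sample-size figure is correct and, secondarily, how much power is left if dropout reaches the planned rate.

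**Working it through.** **Inputs**, all from Sample size {14}: P1 = 0.920, P2 = 0.612, difference 0.308; mean rate p̄ = (0.920 + 0.612)/2 = 0.766, q̄ = 0.234; two-sided α = 0.05; β = 0.20; Zα + Zβ = 2.8; dropout 20%.

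**1. The article's base size.** n = 2 p̄ q̄ (Zα + Zβ)² / (P1 − P2)² = 2 × 0.766 × 0.234 × 7.84 / 0.094864 = 29.63, rounded up to 30. The stated 30 reproduces.

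**2. The article's recruited size.**
- 30 × 1.2 = 36, which matches the stated figure.
- 30 / (1 − 0.20) = 37.5, rounded up to 38 per group, 76 in total.
- From the unrounded base, 29.63 / 0.80 = 37.04, also rounded up to 38, so rounding does not rescue 36.

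**3. What 36 per group provides.**
- After 20% loss: 36 × 0.80 = 28.8 per group, so 28 or 29 patients against 30.
- Loss tolerated while keeping 30: 1 − 30/36 = 16.7%. Measured against the unrounded 29.63 it is 1 − 29.63/36 = 17.7%. Either way it is below 20%.

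**4. Power by the article's own formula**, solved for power: Φ(0.308 / √(2 × 0.766 × 0.234 / n) − 1.96).

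| n per group | Power |
|---|---|
| 28 | 77.7% |
| 28.8 | 78.8% |
| 29 | 79.1% |
| 30 | 80.4% |
| 36 | 87.0% |
| 38 | 88.7% |

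**5. Power by other two-sided methods at α = 0.05.**

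| n per group | Fleiss, no continuity correction | Exact, chi-square test | Exact, Fisher test |
|---|---|---|---|
| 28 | 79.3% | 81.1% | 71.1% |
| 28.8 | 80.5% | not applicable | not applicable |
| 29 | 80.8% | 82.6% | 73.4% |
| 30 | 82.1% | 84.1% | 75.6% |

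Fisher's test falls short of 80% already at 30 per group. That part of its deficit (80 − 75.6 = 4.4 points) comes from the choice of test and not from the dropout step. It is about half of the whole deficit at 28 per group (80 − 71.1 = 8.9) and two thirds at 29 (80 − 73.4 = 6.6).

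**The case against.** The strongest reply is that almost nothing follows from the slip, and much of that reply stands.

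- **A reader might infer that the trial fails to deliver its stated power.** The document does not support this in any material sense. The article's own formula gives 78.8% at 28.8 per group, 1.2 points under 80%. Fleiss gives 80.5%, and exact chi-square power exceeds 81% even at 28.
- **Dropouts need not leave the analysis.** Selection of dataset describes the full analysis set as an intention-to-treat set of randomised patients, with only eligibility errors removed. If dropouts stay in and the assumed rates still apply to them, the set stays near 36 per group and the same formula gives about 87%. This stands for that set. However, Statistical analysis {20} also bases efficacy on the per-protocol set, which requires 80 to 120% compliance and completed case report forms, and 28.8 is the relevant size there. An allowance for dropout also presupposes that dropouts do not count towards the 30.
- **The rate is only approximate.** True, and 16.7% is not far from 20%. But 20% is the only rate given, and 36 is exactly 30 × 1.2, so the word softens the rate without making the calculation right.
- **The shortfall is tiny.** Against the unrounded 29.63 it is 29.63 − 28.8 = 0.83 patients per group. The gap of two per group between 36 and 38 is partly rounding. This bears on severity, not on correctness.
- **The figure is not the power of the primary analysis.** The calculation concerns an effective rate, while Primary outcome measurements names the GERD-Q score at 8 weeks. Statistical analysis {20} also specifies one-sided tests, under which Fleiss power at 28.8 would be about 88%. These are separate issues. They do not correct the dropout figure, but they are a reason to state plainly which comparison any restated power refers to.

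**Conclusion.** The dropout allowance is miscalculated. For 30 per group after 20% loss the number is 38 per group (76 in total), not 36 (72). With 36, about 28.8 per group remain, one to two below the stated requirement, and the plan covers about 17% loss.

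Severity is minor. The cost in power is about one point by the article's own formula, from 80% to about 79%. This rests on three assumptions: dropout reaches 20% in each group, those patients leave the analysis (as in the per-protocol set), and the rates of 92.0% and 61.2% hold. If dropouts remain in the full analysis set on the same rates, there is no loss. The finding supports a corrected statement; it does not support calling the trial underpowered because of this step.

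**What to change.** Keep 72 patients and replace the dropout sentence under Sample size {14} with one that matches the numbers, for example:

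> Recruiting 36 per group allows for about 17% dropout; at 20% dropout about 29 per group remain, with about 79% power by the same formula for the effective-rate comparison.

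The cost is one sentence and a slightly less favourable figure. The total of 72 under Study design and setting {8-9} can stay. No extra patients and no change to design or analysis are needed, which suits a trial that Trial status reports as already recruiting. If the sponsor preferred to keep the 20% allowance as stated, the total would have to be 76, four more patients; the small effect on power does not require that.

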### Recruitment {15}

All the cases will be from outpatients of digestive department in Dongfang hospital, Beijing University of Chinese Medicine, who were clinically diagnosed as NERD, and dialectically belonged to the syndrome of intermingled heat and cold.

### Allocation {16}

The drugs are allocated according to the random coded sequence of the research center and the number of cases. We will designate a research drug administrator. The drug will be distributed by the administrator according to the method of randomization and blinding and registered in the “Clinical Research Drug use record form” after the researchers screen the qualified subjects and wrote the research medical records with informed consent.

### Randomization and blinding {16.17}

The research drugs will be randomly coded according to the randomized scheme of clinical research in Xiyuan Hospital of the Academy of TCM. (1) The method of random allocation: using SAS software to generate random sequences, randomly grouping, and coding drugs; (2) the distribution scheme of hiding and implementing: the sealed envelope method will be used to hide the random sequences.

Blindness will be set for the implementers (doctors) of the study and the subjects (patients). The random code of the drug used will be the unique identification code of the subjects. Each coded drug will be accompanied by an emergency treatment plan in the letter. If emergencies occur in the treatment period, implementers need to know what kind of treatment the patient is receiving. The letter shall be opened in the presence of at least two researchers and collected together with the case report form (CRF) after the end of the trial. Blind leakage or emergency letter opening should not exceed 20% before the end of the trial.

### Consent and assent {26a,27}

Implementers will explain the purpose of the study and benefits/risks to participate who volunteer to join the research group and sign an ICF. The main investigator will be responsible for obtaining informed consent. All the medical records will be kept in Dongfang hospital. It will be allowed to access medical records of patients for researchers, research authorities, and ethics committees. The specimens collected in the test will be destroyed after use. Any public report on the results of this study will not disclose the personal information of the patients.

### Interventions {11}

#### Intervention description {11a}

TCM group was given HWJNR with omeprazole enteric-coated tablets placebo; western medicine group was given omeprazole enteric-coated tablets with HWJNR placebo. The course of treatment is set for 8 weeks. Medication method and dose were as follows: omeprazole enteric-coated tablets/placebo: 20 mg, once a day, half an hour before breakfast; HWJNR/placebo: twice a day, one bag at a time, half an hour after breakfast and dinner. For production of formula placebo: the TCM placebo is made by Beijing Kangrentang Pharmaceutical Co., Ltd., according to the preparation process of HWJNR. The shape, color, gas, and taste will be similar to HWJNR after adding the same kind and equal amount of excipients. Finally, 5% of the original unit treatment drug is added to correct color and taste.

### Adverse reaction {11b}

The change or discontinuation of the intervention will be determined by the performance of the participants after taking the drug. The researcher will truthfully reflect the changes of the condition during the study period. Our first priority is to protect the safety of the subjects. If the symptoms of gastroesophageal reflux such as reflux and heartburn have not been effectively relieved, hydrotalcite chewable tablets (Daxi) will be used for temporary treatment, and the total dosage of hydrotalcite chewable tablets in the two groups will be counted at the end of the trial.

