### Combined use of drugs {11d}

During the study period, drugs with the same efficacy as the study drugs or related to the treatment of NERD will be prohibited to reduce intervention. If the subjects take drugs to control chronic diseases, such as hypertension and diabetes, they should truthfully and detailedly record the medication in the trial, including drug name (or other treatment name), dosage, frequency, and time of use.

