### Outcomes {12}

#### Primary outcome measurements

##### GERD-Q scale score

GERD-Q scale is the most recognized and widely used special scale for GERD diagnosis in the world. In addition to diagnosing GERD, it can also evaluate the impact of GERD on quality of life and monitor the effect of treatment with high accuracy. A trained evaluator will record the evaluation at baseline, week 4, and week 8, fill out the GERD-Q questionnaire, and calculate the total score, frequency score, and degree score of GERD-Q symptoms. In the study, the score of GERD-Q scale after 8 weeks treatment will be used as the main outcome index.

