##### Selection of dataset

Full analysis set (FAS): FAS refers to the intention-to-treat (ITT) analysis of all patients who have been randomized into groups and assigned to random numbers (called willing treatment groups). Errors that do not meet the inclusion criteria or exclusion criteria are excluded.Per-protocol set (PPS): PPS refers to the statistical analysis of all cases that is in accordance with the clinical observation plan (Compliance with medication ranging from 80 to 120% will be eligible for the protocol analysis set). Subjects will not take prohibited drugs during the observation period, and completed the CRF requirements.Safety set (SS): Safety data should include all subjects who have received at least one treatment and at least one safety assessment after randomization.

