### Statistical analysis {20}

Efficacy analysis will be performed based on both FAS and PPS patients. Safety analysis includes all randomized participants who take at least one bag of HWJNR and have data for safety assessment. Comparing the healthy control group with the traditional Chinese medicine group, we will study the composition of the intestinal flora and the expression of metabolites in patients with NERD and the healthy group. And it will also reveal the mechanism of action and advantages of HWJNR in the treatment of NERD patients.

Changes from baseline to post-treatment in GERD-Q, SF-36, PRO, and syndrome score of TCM will be analyzed using analysis of covariance with associated 95% confidence intervals. All the analysis results will be generated by SPSS 25.0 software. Repeated measurement data are expressed by mean ± standard deviation, intra-group comparison is performed by analysis of variance of repeated measurement data, and inter-group comparison is by multivariate analysis of variance (MANOVA). *P* ≤ 0.05 indicates that the difference is statistically significant. Unilateral test will be used in all statistical tests, and the significance level *P* ≤ 0.05. The arithmetic mean, standard deviation, median, minimum, and maximum will be calculated according to the data distribution. Counting data will be used to calculate the number and percentage of cases.

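### The only stated use of the rescue hydrotalcite data is a raw group total, which unequal dropout can distort and which cannot show how far rescue affected the week-8 GERD-Q comparison

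*Protocol article*

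**What the plan says.** All references are to the Protocol article.

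- **Adverse reaction {11b}:** when reflux or heartburn is not adequately controlled, "hydrotalcite chewable tablets (Daxi) will be used for temporary treatment". The same sentence gives the only stated use of the data: "the total dosage of hydrotalcite chewable tablets in the two groups will be counted at the end of the trial".
- **GERD-Q scale score (primary outcome):** "the score of GERD-Q scale after 8 weeks treatment will be used as the main outcome index".
- **Statistical analysis {20}:** "Changes from baseline to post-treatment in GERD-Q, SF-36, PRO, and syndrome score of TCM will be analyzed using analysis of covariance". Efficacy is analysed in both the full analysis set and the per-protocol set. Rescue is not mentioned.
- **Outcomes {12} and Safety outcomes:** hydrotalcite use is not listed.
- **Combined use of drugs {11d}:** "drugs with the same efficacy as the study drugs or related to the treatment of NERD will be prohibited to reduce intervention". No exception is written for hydrotalcite.
- **Selection of dataset, per-protocol set:** "Subjects will not take prohibited drugs during the observation period, and completed the CRF requirements".
- **Compliance {11c}:** a daily CRF covers study medication and symptoms. It does not mention hydrotalcite.

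**The concern.** Rescue use here is a consequence of poor symptom control, and it treats the symptoms that GERD-Q scores. That raises two problems.

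First, the measure that the protocol names is weak. A group total depends on how many patients stayed and for how long, as well as on how much each one took. Patients without relief are plausible leavers, so the arm with worse control could show the smaller total.

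Second, if one arm needs more rescue, its week-8 scores improve partly through the antacid and the arms move closer together. A small GERD-Q difference could then mean similar treatments, or different treatments evened out by rescue. A sound measure of rescue would help a reader tell these apart; a raw group total does not.

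**Working it through.** **Inputs from the documents.** Sample size {14}: 30 per group before dropout, about 20% dropout, 36 per group recruited. Interventions {11}: 8 weeks of treatment, that is 56 days. The documents give no expected rescue use, no split of dropout by arm and no standard deviation for GERD-Q.

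**The plan's own figure.** 2 × 0.766 × 0.234 × 2.8² ÷ 0.308² = 29.63, rounded up to 30. Then 30 × 1.20 = 36. Both reproduce. The 36 is used below.

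**Step 1: distortion of a group total.** With identical daily use per patient, each arm's total is proportional to its patient-days on treatment. Assume that the 20% loss (0.20 × 36 = 7.2, taken as 7) falls in one arm only.

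| Case | Patient-days | Total against full arm |
|---|---|---|
| No dropout | 36 × 56 = 2016 | reference |
| 7 leave at day 28 | 2016 − 7 × 28 = 1820 | −9.7% |
| 7 leave at day 14 | 2016 − 7 × 42 = 1722 | −14.6% |

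Less extreme splits, still averaging 20% overall:

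| Dropout by arm | Ratio of totals, leaving at day 28 | Ratio of totals, leaving at day 14 |
|---|---|---|
| 20% and 20% | 1.00 | 1.00 |
| 15% and 25% | 1864.8 ÷ 1764.0 = 1.06 | 1789.2 ÷ 1638.0 = 1.09 |
| 10% and 30% | 1915.2 ÷ 1713.6 = 1.12 | 1864.8 ÷ 1562.4 = 1.19 |

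The distortion therefore needs dropout, or its timing, to differ between arms. With equal dropout at equal times there is none.

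**Step 2: movement of the GERD-Q difference.** Loss of difference = (rescue proportion in arm A − rescue proportion in arm B) × points by which rescue lowers a user's score. Assume 40% and 15%, and 1 to 3 points: 0.25 × 1 = 0.25 up to 0.25 × 3 = 0.75 points.

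The planning rates give a rough check on the size of that gap: "the effective rate of NERD in the TCM group was P1 = 92.0" per cent and "The NERD effective rate of the western medicine group was P2 = 61.2" per cent. If every patient not effectively treated took rescue (again an assumption), the proportions would be 1 − 0.612 = 0.388 and 1 − 0.920 = 0.080. The gap would be 0.308, and the loss 0.31 to 0.92 points.

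**Step 3: the per-protocol set.** Hydrotalcite is permitted under {11b} for reflux symptoms. Drugs related to NERD treatment are prohibited under {11d} with no exception written, and users of prohibited drugs fall outside the per-protocol set. Read literally, rescue users leave that set. On the same assumption as in Step 2, that is 0.388 × 36 ≈ 14 patients in one arm and 0.080 × 36 ≈ 3 in the other, a selection on treatment failure. If hydrotalcite is exempt, neither analysis set takes account of rescue. The text does not say which reading applies.

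**The case against.** The strongest reply is that the sentence sits in the intervention section and may only describe data collection. Handling of rescue and sensitivity analyses are often left to a statistical analysis plan, which is not shown here. Comparing outcomes regardless of rescue is also a legitimate treatment-policy question, and pulling the arms together is conservative for a superiority claim. Every magnitude above is assumed.

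Much of this stands. Analysing GERD-Q regardless of rescue is not an error, and silence about a sensitivity analysis would not be a finding by itself. What remains is that the protocol does name a measure, and the one it names is poor. Conservatism also does not help a reader who has to interpret a small or null difference against an active comparator.

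Three stronger readings are tempting, and the documents do not support them.

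- *The total mixes in antacid taken after treatment.* Study design and setting {8-9} uses the same end-of-trial phrase for outcomes last assessed at week 8, and medication at months 1 and 3 is recorded separately as the recurrence index. The text points to week 8.
- *Rescue has no bearing on any efficacy analysis.* It may remove patients from the per-protocol set, as Step 3 shows.
- *The data for a better measure already exist.* Counting a total implies some individual record, but no section says that hydrotalcite is entered by date.

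**Conclusion.** The point holds as a moderate one. The only stated summary of rescue is a group total without a patient or day denominator. It would be about 10% to 15% too low for an arm that alone lost 7 of 36 patients at week 4 or week 2, and undistorted if dropout matched in number and timing. Unequal rescue can also shrink the week-8 GERD-Q difference. The range of 0.25 to 0.75 points rests wholly on assumed rescue rates and effects, and without a GERD-Q standard deviation or margin it cannot be called large or small. The sections on rescue, prohibited drugs and the per-protocol set leave the status of hydrotalcite unresolved and must be reconciled. A reader might infer that the primary analysis is invalid; the documents do not support that. This point passes no judgement on the rescue rule itself.

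**What to change.** 1. Replace the group total. Record hydrotalcite with dates in the daily CRF, derive each patient's use per treatment day over weeks 1 to 8, with that patient's own days on treatment as denominator, and compare it between arms as a named secondary outcome. This removes the effect of unequal exposure time. It does not remove selection if the heaviest users leave early, so report dropout by arm beside it.
2. Keep the primary GERD-Q analysis regardless of rescue, and say so.
3. Add one sensitivity analysis in which patients who took rescue shortly before the week-8 GERD-Q count as unimproved and keep their baseline score. Set the window to the questionnaire's recall period, which the documents do not give.
4. Reconcile Adverse reaction {11b}, Combined use of drugs {11d} and Selection of dataset on whether permitted hydrotalcite counts as a prohibited drug for the per-protocol set.

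The cost is small: a dated rescue field in the CRF if there is none, one more secondary outcome and one sensitivity analysis. Trial status reports 10 volunteers recruited at submission; for patients enrolled before such a field is added, dated use may be incomplete and should be reported as such.
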